### Statistical analysis

2.7

The data will be presented as the mean ± standard deviation. The independent *t* test and chi-square test will be used to evaluate and compare the baseline patient characteristics between the experimental and control groups. The independent *t* test and McNemar test will be used to compare the differences between 2 groups. Repeated-measures analysis of variance, generalized estimating equations, and the paired *t* test will be used for comparisons between the 2 study groups. All analyses will be performed using SPSS for Windows, version 22 (Statistics 22, IBM Corp., Armonk, NY). A *P* value < .05 will be considered statistically significant.

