**Methods::**

Fifteen men with opioid use disorder on methadone maintenance treatment have been enrolled from an addiction treatment center as an experimental group in this case-controlled study. This group is receiving laser meridian massage on the back, including the Bladder meridian and Governor Vessel, 3 times weekly for 4 weeks. An age-matched control group that does not receive laser meridian massage has also been enrolled. Urinary morphine levels are being checked before and after 2 and 4 weeks of treatment. Subjects are requested to self-report their number of episodes or days of heroin use and 0 to 10-point visual analogue scale scores for heroin craving/refusal to use heroin during the previous week before and after 2 and 4 weeks of treatment. Quality of life will be reported using the Short Form-12v2 before and after 4 weeks of treatment. Pulse diagnosis will be recorded and heart rate variability calculated after one single treatment session. The baseline patient characteristics will be compared between the experimental and control groups using the independent *t* test and Chi-square test. Data are compared between the 2 groups using repeated-measures analysis of variance, generalized estimating equations, and the paired *t* test.

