### Study design

2.2

This case-controlled study is being performed in the Department of Psychiatry and Chinese Medicine at Kaohsiung Chang Gung Memorial Hospital. The study was started in February 2019 and will continue until February 2020. Subjects recruited from our institution's addiction treatment center are being allocated to the experimental group (laser meridian massage plus methadone maintenance treatment, n = 15, expected). The study participants will receive 12 sessions of laser meridian massage three times weekly for 4 weeks. An age-matched control group of subjects who do not receive laser meridian massage (methadone maintenance treatment only, n = 15, expected) will also be enrolled. The study design is shown in Figure 1.

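### The paired t test and the McNemar test are assigned to comparing two groups of different men, and no listed test is named as the one that decides

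*Protocol article*

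**What the plan says.** Section 2.7 (Statistical analysis) states that, alongside the independent t test, the "McNemar test will be used to compare the differences between 2 groups". The next sentence reads: "Repeated-measures analysis of variance, generalized estimating equations, and the paired *t* test will be used for comparisons between the 2 study groups". The Methods part of the abstract says the same of the paired t test: "Data are compared between the 2 groups using repeated-measures analysis of variance, generalized estimating equations, and the paired *t* test". No sentence gives either paired test a within-person, before-after role.

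Section 2.2 (Study design) describes the arms as "laser meridian massage plus methadone maintenance treatment, n = 15, expected" and "methadone maintenance treatment only, n = 15, expected". The comparison arm is "An age-matched control group of subjects who do not receive laser meridian massage". The article does not say whether each treated man has one designated control or whether the groups are merely similar in age.

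Section 2.7 compares baseline characteristics with the independent t test and the chi-square test. It sets a significance threshold of P < .05 without saying which of the listed tests decides.

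**The concern.** The paired t test and the McNemar test work on linked pairs of observations. Here the natural pairs are two visits by the same man. A treated man and a control man form a pair only if they were individually matched, and the article does not say they were.

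If there are no such pairs, an analyst told to run a paired t test on these data will most naturally run it before versus after, separately in each arm. Each run answers whether that arm changed. Neither answers whether the arms changed differently. The men are all on methadone, some for as little as one month (section 2.3), so both arms could improve over four weeks without any laser effect. At stake is whether a significant P value from the laser arm alone could be reported under a heading that promises a comparison between groups.

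**Working it through.** **1. The plan's own figure.** Section 2.4 gives N = 28 for a 2-way repeated-measures ANOVA with f = 0.25, α = 0.05 and power 0.80. The check uses the group-by-time interaction with k = 2 groups and m = 3 times (before, week 2, week 4). It assumes sphericity and a correlation between visits of ρ = 0.5, which the article does not state.

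- λ = f²·N·m/(1−ρ) = 0.0625 × 28 × 3 / 0.5 = 10.5
- df = (k−1)(m−1) = 2 and (N−k)(m−1) = 26 × 2 = 52
- Power = 0.812, so 28 reproduces. With ρ = 0.3 the answer is 38, and with ρ = 0.7 it is 18.

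The sample size is therefore consistent with a genuine between-group comparison over time. It does not rest on the paired t test or the McNemar test.

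**2. Before-after reading of the paired t test.** Inputs: n = 15 per arm (section 2.2), two-sided α = 0.05 (section 2.7), no treatment effect, and the same mean change d in both arms, in units of the SD of change. The range of d is assumed.

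- One-arm rejection probability: p = P(|T| > 2.145), where T is noncentral t with 14 df and noncentrality d√15.
- The arms are independent, so P(laser significant, control not) = p(1−p).

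| Shared change d | p, one arm | p(1−p) |
|---|---|---|
| 0 | 0.050 | 0.050 × 0.950 = 0.048 |
| 0.3 | 0.192 | 0.192 × 0.808 = 0.155 |
| 0.4 | 0.303 | 0.303 × 0.697 = 0.211 |
| 0.55 | 0.509 | 0.509 × 0.491 = 0.250 |
| 0.75 | 0.771 | 0.771 × 0.229 = 0.177 |
| 1.0 | 0.949 | 0.949 × 0.051 = 0.048 |

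The product p(1−p) cannot exceed 0.25, reached at p = 0.5, so 0.55 SD sits practically at the maximum. In the first row, significance in either direction is counted; in the direction of benefit alone the figure is 0.024. For d of 0.3 and above the direction makes almost no difference.

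If the laser arm's P value were read alone, the false-positive rate would be p itself: 14.7% at 0.25 SD, 43.8% at 0.5 SD, 77.1% at 0.75 SD and 94.9% at 1.0 SD. An independent t test of change stays at 5% throughout.

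**3. Before-after reading of the McNemar test.** Suppose that in both arms 5% of men turn from negative to positive and 30%, 40% or 50% turn the other way (all assumed). The exact test within one arm of 15 is then significant towards benefit in 16.7%, 37.8% or 59.6% of trials, again with no treatment effect.

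**4. Literal, across-arm reading.** Suppose treated and control men are paired and the paired t test is run across arms. In 100,000 simulated trials with n = 15, type I error is about 5% at pair correlations of 0, 0.1 and 0.3. With zero correlation, power at a difference of 0.8 SD is 0.53, against 0.56 for the independent t test. With a pair correlation of 0.3, the independent t test becomes conservative (type I error 2.1%) and the paired test is more powerful (0.68 against 0.57).

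**The case against.** The strongest reply is that a sound comparison is already planned. Section 2.7 names the independent t test, repeated-measures ANOVA and generalized estimating equations for comparing the groups, and section 2.4 sizes the trial on repeated-measures ANOVA. This stands. A reader might infer that the trial has no valid between-group analysis; the text does not support that.

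Second, the article nowhere says that benefit will be concluded from a significant laser arm and a non-significant control arm. This also stands. A reader might take 15% to 25% as the trial's false-positive rate. That would require a decision rule the article does not state and an improvement it does not quantify, and the figure falls to about 5% at either end of the range. On the literal across-arm reading, the paired t test holds its level.

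Third, a reader might infer that the paired and unpaired tests invalidate each other, so that one set must give wrong answers. That is too strong. If men were individually matched on age, the pair correlation may be small and an unpaired analysis would be at worst conservative. If they were not, pairing across arms would cost a little power and make the result depend on an arbitrary ordering, but would not inflate type I error.

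What the reply does not remove is the wording. Two tests are given a between-group role that the described design does not support, in section 2.7 and, for the paired t test, again in the abstract. Naming valid methods beside them does not say which result counts. This is something the article states, so it is not a detail left to an analysis plan.

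**Conclusion.** The point holds as a misassignment of two tests, together with the absence of a deciding one. As described, the groups are independent, and section 2.7 itself treats them so; the paired t test and the McNemar test then have no between-group function.

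The harm is conditional. It arises only if a within-arm result is read as a treatment effect. In that case the misleading pattern occurs in about 5% to 25% of null trials, depending on a shared improvement assumed to lie between 0 and 1.0 SD of change, with 15 men per arm and independent arms. Because the article labels these tests as between-group comparisons and applies the same P < .05 to every test, nothing in the text prevents that reading. The sample size is not affected.

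**What to change.** In section 2.7 and the abstract:

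- Remove the paired t test and the McNemar test from the between-group comparisons, and limit them to describing change within a group.
- State whether the age matching is individual or at group level. The article does not settle this, so the sponsor must. If it is individual, use methods that respect the pairs throughout, including at baseline.
- Base any claim of benefit only on the between-group comparison already planned: the group-by-time term of the repeated-measures ANOVA or of the generalized estimating equations. Name which of the two decides.
- If a binary outcome is analysed (section 2.6 names urinary morphine levels, not a positive/negative result), compare independent groups with Fisher's exact test, logistic regression or generalized estimating equations instead of McNemar.

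The cost is wording only: no new data and no change to the planned 28 (30 with dropout).

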### Sample size

2.4

A sample size of 28 was calculated to be needed based on 2-way repeated-measures analysis of variance with a medium effect size of 0.25, a significance level (α) of 0.05, and a desired power (1−β) of 0.80.^[13]^ Anticipating a 7% dropout rate, a total of 30 study participants will need to be recruited.

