### Outcome measurements

2.6

Outcome measures will include subjective reporting of heroin use and quality of life and objective urinary morphine levels. The primary outcomes are urinary morphine levels and self-reported times or days of heroin use during the previous week before and after 2 and 4 weeks of treatment. The secondary outcomes are self-reported visual analogue scale (VAS) scores for heroin craving/refusal to use heroin (0–10 points) in the previous week before and after 2 and 4 weeks of treatment and quality of life using the Short Form-12v2 (SF-12v2) before and after 4 weeks of treatment. The participant's pulse diagnosis and heart rate variability after one single treatment session are also being recorded.

A VAS score of 0 for heroin craving indicates no heroin craving and a score of 10 indicates the strongest possible heroin craving. A VAS score of 0 for refusal to use heroin indicates no refusal and a score of 10 indicates total refusal. The SF-12v2 Health Survey is a multipurpose, short-form health instrument containing 12 questions that yields an 8-scale profile of functional health and well-being (Physical Functioning [PF], Role-Physical [RP], Bodily Pain [BP], General Health [GH], Vitality [VT], Social Functioning [SF], Role-Emotional [RE], Mental Health [MH]), as well as two psychometrically-based physical and mental health summary measures and a preference-based health utility index. The PRO CoRE, which is part of the Smart Measurement System suite of products and Optum's upgrade to the QualityMetric Health Outcomes scoring software, will be used to score the SF-12v2 Health Survey.

The reasons for patients not completing their follow-up visits or dropping out of the study, such as adverse events/intercurrent illnesses, suboptimal response to therapy, failure to return for follow-up, failure to meet the selection criteria at entry, other protocol violations, and refusal to receive treatment, are recorded, as are potential adverse events.

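### Repeated-measures ANOVA discards any man with a missed visit, and an uncorrected robust GEE would be too liberal at 15 men per arm; one mixed model should decide for continuous outcomes

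*Protocol article*

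**What the plan says.** The Statistical analysis section (2.7) names "Repeated-measures analysis of variance, generalized estimating equations, and the paired" *t* test for comparisons between the groups, run in SPSS 22 at P < .05.

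The Sample size section (2.4) rests on the first of these methods: "A sample size of 28 was calculated to be needed based on 2-way repeated-measures analysis of variance". The inputs behind that figure are a medium effect (0.25), α = 0.05 and 80% power. On losses, the section adds: "Anticipating a 7% dropout rate, a total of 30 study participants will need to be recruited".

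The Outcome measurements section (2.6) sets the primary outcomes at three times: baseline, week 2 and week 4. Its examples of reasons for incomplete follow-up, all to be recorded, include "adverse events/intercurrent illnesses, suboptimal response to therapy, failure to return for follow-up".

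The Study design section (2.2) gives the experimental arm as "laser meridian massage plus methadone maintenance treatment, n = 15, expected". The controls, also 15 expected, stay on methadone maintenance without laser.

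**The concern.** Classical repeated-measures ANOVA needs every visit from every man. One who attends at baseline and week 2 but not at week 4 contributes nothing, although two of his three values are known. The paired *t* test is milder, since it loses a man only if one of its own two visits is missing. If men leave because they are doing badly, those who remain look better than the group that was enrolled. Both arms can lose men, but only the laser arm has 12 extra sessions to abandon, so unequal loss is possible and would favour laser.

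GEE avoids the loss of partial records but can have a different weakness. Its usual robust variance is justified for many clusters, and here there are 15 per arm. At stake are a modest bias in the primary comparison from one method and an excess of false positives from the other.

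**Working it through.** **1. The plan's own figure.** Inputs from section 2.4: f = 0.25, α = 0.05, power 0.80. There are 2 groups and 3 visits. Correlation ρ = 0.5 and sphericity are assumptions, as the article gives neither. For the group-by-time interaction:

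- λ = f² × N × 3/(1 − ρ) = 0.0625 × 28 × 3/0.5 = 10.5, with df 2 and (28 − 2) × 2 = 52.
- Power is 0.812 at N = 28 and 0.778 at N = 26. So 28 is reproduced.

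The dropout allowance is 30 × 0.07 = 2.1 men, leaving 27.9. At the planned dropout the completer ANOVA keeps power near 0.81.

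**2. Completer bias with no true effect.** Assume unit SD at each visit, correlation 0.5 between any two visits, and loss of the laser-arm men with the worst change at week 2. The SD of a change is √(2 × (1 − 0.5)) = 1. The two largest of 15 standard normal values have expectations 1.736 and 1.248.

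| Laser men lost | Week-2 bias | Week-4 bias (half carries over) |
|---|---|---|
| 1 | 1.736/14 = 0.12 SD | 0.06 SD |
| 2 | (1.736 + 1.248)/13 = 0.23 SD | 0.11 SD |

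Half carries over because the covariance of the two changes is 0.5 and the variance is 1. The standard error of the week-4 contrast is √(2/15) = 0.37 SD. In simulation, the completer ANOVA's false-positive rate rises from about 5% with no loss to about 9% with the two worst laser-arm responders lost.

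Other mechanisms give other values at week 4:

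- With first-order autoregressive correlation 0.5, the carry-over is 0.75, giving 0.75 × 0.124 = 0.09 SD and 0.75 × 0.230 = 0.17 SD.
- With dropout merely more likely after a poor week-2 change (same autoregressive correlation), the bias is 0.05–0.08 SD at 7% loss in the laser arm and 0.09–0.13 SD at 13% (2 of 15).
- With equal correlations and dropout driven by the week-2 level rather than the change, it is about zero.

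**3. GEE at 15 per arm.** With complete normal data and a mean for each group at each visit, the robust variance of the group contrast is the usual one multiplied by 14/15, and it is referred to chi-square.

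- 1 df (week-4 contrast): the test rejects when |t₂₈| > 1.960 × √(14/15) = 1.893, which has probability 6.9%.
- 2 df (interaction): it rejects when F(2, 27) > 5.991 × (14/15) × 27/56 = 2.696, which has probability 8.6%.

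Simulation gives 6.9% and 8.4%. For the 2-df test, other outcome types gave 10.5% (overdispersed counts), 6.6% (binary) and 6.4% (skewed lognormal). At 100 per arm it gave 4.9%, so the excess comes from the small number of clusters. At 15 per arm, an unbiased covariance with an F or t reference gave 4.8% (2 df) and 5.0% (1 df). A bias-corrected sandwich still referred to chi-square gave 5.9%.

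**4. Does the remedy work?** Use the setting of step 2 with two men lost. If their week-2 values were seen before they left, a likelihood estimate on all visits has week-4 bias of about zero, against 0.11 SD for completers. If their week-2 values are missing too, week-2 bias falls only from 0.23 to 0.18 SD.

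**The case against.** The case against is that this is a condensed article naming standard methods. Variance estimators, degrees of freedom and missing-data rules are commonly left to a fuller plan, and each method has only one of the two defects: ANOVA holds its size on complete data (4.9%), and GEE keeps partial records. The point about absent detail is right, and no finding is made of it. The choice of repeated-measures ANOVA, however, is stated in the text and carries the sample size.

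Four stronger readings are tempting, and the documents do not support them:

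- **That the plan implies one-sided, outcome-related dropout.** Both arms receive methadone, so poor response to therapy can occur in either. Section 2.6 gives examples of reasons to be recorded, without frequencies or a split by arm.
- **That the bias is large or the power collapses.** Losing three or four laser-arm men gives 0.33 or 0.42 SD at week 2, and power falls to 0.65 with 20 completers. But 20 completers means losing 10 of 30 men, and even three or four exceeds the 2.1 planned.
- **That GEE as planned rejects too often.** No variance estimator or test is named. In the same normal setting, a model-based exchangeable variance gave 5.8% and a score-type test 4.8%.
- **That a mixed model cures the problem.** It does so only when the outcome that drove the dropout was observed.

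**Conclusion.** The concern holds in a limited form. Repeated-measures ANOVA discards usable visits in a trial that expects to lose about 2 of 30 men. Its cost within the planned dropout is modest: no material loss of power and, if the one or two men lost are the worst early responders in the laser arm, a week-4 bias of about 0.06 to 0.11 SD in favour of laser. Other assumed mechanisms gave from about zero to 0.17 SD. All of these are below half the standard error of 0.37 SD.

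The GEE excess, about 7% to 8.5% instead of 5% for normal outcomes, is conditional on an uncorrected robust Wald chi-square test. The correlation of 0.5 and every dropout mechanism are assumptions. A change is still worth making, because a better method exists in the software already chosen.

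**What to change.** In section 2.7, replace repeated-measures ANOVA by one linear mixed model fitted by REML, with group, time and group-by-time, unstructured covariance and Satterthwaite degrees of freedom. Use all available visits of every enrolled man in the group in which he was enrolled, whatever sessions he attended. State that this is the deciding analysis for continuous outcomes. SPSS MIXED can fit it.

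Where a count or binary link is needed, such as for times or days of heroin use, use GEE with a small-sample-corrected variance and a t or F reference.

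Add a sensitivity analysis that scores missing post-baseline urine as heroin use, to cover loss whose cause was never observed. Because the outcome is a urinary morphine level, the cut for a positive result has to be fixed beforehand.

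The cost is wording and slightly more analysis, with no extra men or visits. The corrected GEE may need software other than SPSS 22.

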### Data monitoring

2.8

A data monitoring committee (DMC) is not needed because laser meridian massage is a routine and noninvasive intervention.

## Discussion

3

According to the 2019 report of the United Nations Office on Drug and Crime, the global prevalence of opiate (heroin and opium) use was estimated to be 0.6% in the population aged 15 to 64 years in 2017 (29.2 million); furthermore, the number of past-year opiate users globally was 50% higher than the previously estimated 19.4 million in 2016.^[14]^ The prevalence of heroin use was estimated at 0.23% in the population aged 12 to 64 years in 2014 (42,428, all adults) in Taiwan.^[15]^ Addiction to opiates such as heroin is of great importance because it has such serious sequelae, including high mortality and crime rates. Moreover, impaired cortical plasticity has been detected in heroin addicts, which might account for the addiction scores in these individuals (e.g., craving, relapse) from the perspective of psychomotor stimulant theory or the spiral theory of addiction.^[16]^ Treatment of OUD includes a set of pharmacologic and psychosocial interventions aimed at reducing or ceasing opioid use, preventing future harms associated with opioid use, and improving quality of life and well-being.^[3]^ Pharmacologic strategies have not been successful in management of withdrawal symptoms in heroin addicts; therefore, it is time to investigate the potential benefits of complementary and alternative medicine, which has a long history in the treatment of disease and few side effects.^[17]^

Acupuncture can exert an antinociceptive effect by accelerating the production and release of opioid peptides in the central nervous system. The antinociceptive effect is frequency-dependent, with low-frequency (2-Hz) stimulation accelerating production of endorphin and encephalin and high-frequency (100-Hz) stimulation upregulating the dynorphin level.^[18,19]^ High-frequency (100-Hz) electroacupuncture is effective in reducing withdrawal symptoms, and there is a suggestion that dynorphin suppresses symptoms of withdrawal at the spinal level. The effects of 100-Hz electroacupuncture may include activation of brain-derived neurotrophic factor in the ventral tegmental area, while multiple 100-Hz stimulation may have a cumulative effect related to acceleration of dynorphin synthesis and downregulation of cAMP response element-binding protein.^[20]^ Furthermore, electroacupuncture could effectively alleviate symptoms of opioid craving and depression, and transcutaneous electrical stimulation of acupoints may help to improve symptoms of insomnia and anxiety.^[21]^

In comparison with traditional acupuncture for obtaining qi, laser acupuncture is not related to somatosensation but has the advantage of being noninvasive and aseptic. Furthermore, no heat is generated during the procedure, making laser acupuncture painless and safe.^[22]^ Laser acupuncture integrates the positive effects of both acupuncture and low-level laser therapy.^[12]^ Laser meridian massage is the application of laser acupuncture. Selection of the meridians for detoxification has been extensive. The meridians that include most acupoints are the Governor Vessel (23.5%) and Bladder meridian (14.7%).^[23]^ Therefore, laser meridian massage is expected to be an effective treatment for patients with OUD on methadone maintenance treatment.
